## Abstract

**Background:**

Treatment of overweight and obesity through body weight reduction has been monumentally ineffective as few individuals are able to sustain weight loss. Rather than treating weight gain once it has become problematic, prevention of weight gain over time may be more effective.

**Objective:**

The aim of this research is to preclude the burden of adult obesity in women by identifying the determinants of weight gain prevention. The objective of this randomized controlled trial (RCT) is to compare a weight gain prevention intervention delivered by the registered dietitian versus counselor.

**Methods:**

This is a 12-month parallel-arm weight gain prevention RCT designed to increase self-efficacy, self-regulation, outcome expectations and family and social support through the use of a nutrition education intervention in women, aged 18-45 years, from the Urbana-Champaign (Illinois, USA) area. Women have been randomized to registered dietitian, counselor or wait-list control groups (August 2014) and are undergoing weekly nutrition education sessions for four months, followed by monthly sessions for eight months (through August 2015). Outcome measures, including: (1) dietary intake, (2) physical activity, (3) anthropometric and blood pressure measurements, (4) biochemical markers of health, (5) eating behaviors and health perceptions, and (6) mediators of behavior change, were collected before the intervention began (baseline) and will be collected at 3, 6, 9, and 12 months of the study.

**Results:**

In total, 87 women have been randomized to intervention groups, and 81 women have completed first week of the study. Results are expected in early 2016.

**Conclusions:**

This RCT is one of the first to examine weight gain prevention in women across normal, overweight, and obese body mass index categories. Results of this research are expected to have application to evidence-based practice in weight gain prevention for women and possibly have implication for policy regarding decreasing the encumbrance of overweight and obesity in the United States.

## Introduction

### Adult Weight Management

Small weight gains over time, around 1-2 pounds per year [1,2], contribute to the development of overweight and obesity. Once established, obesity is difficult to treat [3], as reduction of excess body weight is rarely effective in the long term. Short-term weight loss can be achieved by a variety of methods, but few of these approaches are sustainable and effective in facilitating permanent weight loss [4-10]. On average, individuals adhere to weight loss programs for approximately six months [11]; following weight loss, most individuals regain half of the weight lost within one year, and return to baseline weight within 3-5 years [11-13]. Weight gain prevention, on the other hand, avoids the difficulties that may accompany weight loss and its maintenance and offers an alternative option for weight management.

To reduce disease risk and improve overall health, effective weight gain prevention is essential; however, few interventions have successfully examined weight gain prevention and little is known about the determinants of and strategies for preventing weight gain over the long term. Much of the existing research has focused on treatment of overweight and obesity through reduction of excess body weight [14,15] or prevention of weight regain following weight loss [16-20].

### Weight Gain Prevention

In the first weight gain prevention trial, normal weight adults, aged 25-74 years, were randomized to an untreated control group or a treatment group that received monthly newsletters plus a financial incentive for weight maintenance for one year [21]. The treatment group experienced an average weight loss of 1 kg, which was significantly different from the control group; with the treatment effect being stronger in men than women [21]. Building upon the Pound of Prevention (POP) work, 3-year weight gain prevention in adults, aged 20-45 years, was investigated [22,23]. Participants were randomized to a no-contact control group or to one of two education groups that received nutrition education via monthly newsletters and semiannual nutrition and exercise classes. One education group received a lottery incentive for participation. Significant differences in weight gain between the control and education groups were not found, although weight-related behaviors did improve in participants receiving education [22,23].

The Shape Program was a medium-intensity behavioral intervention in overweight and class I obese premenopausal black women that included weekly self-monitoring, monthly counseling calls, tailored skills training and a YMCA gym membership and was compared to usual care that included newsletters covering general wellness topics every six months during the 18-month study [24]. After one year, weight loss was significantly greater in the intervention group; these changes were sustained at 18 months. No significant differences in waist circumference, blood pressure, glucose or lipid levels between the intervention and usual care groups were observed at any measurement point during the study [24]. Levine and colleagues [25] randomized normal weight and overweight women to a clinic-based group, a correspondence group or a control group for 24 months. During three years, the intervention had no influence on weight gain in either group; however, age, dieting status, and feelings of hunger were found to be predictive of weight gain.

The Groningen Overweight and Lifestyle (GOAL) study examined weight gain prevention in overweight and obese men and women with hypertension and/or dyslipidemia in the Netherlands by comparing the effects of lifestyle counseling by a nurse practitioner to usual care from a general practitioner during a 1-year period [26]. No significant differences were observed in weight change between groups at one year or after three years [26,27]. Study of Novel Approaches to Weight Gain Prevention (SNAP) is the most recently published intervention [28]. Two novel self-regulation approaches to weight gain prevention—small consistent changes and large periodic changes—were compared to a minimal treatment control for an average of three years of follow-up. Results of this study have not yet been published [28]. Without complete knowledge of the determinants of and strategies for weight gain prevention, public health will remain at risk for complications and costs related to overweight and obesity. Weight gain prevention offers a primary strategy for weight management and obesity prevention [24,26].

Women who previously participated in a weight-loss intervention identified gender-specific life transitions and stressors, including pregnancy, post pregnancy, family responsibilities, health status changes, and aging as precipitators of weight gain [29]. Young adulthood and perimenopause appear to be critical intervals for weight gain [30-32]; therefore, weight gain prevention efforts should target these lifespan stages, specifically in women.

### Aims and Objectives

The current study aims to identify determinants of weight gain prevention in young adult and midlife premenopausal women through a 1-year weight gain prevention intervention that includes nutrition education. We hypothesize that compared to a wait-list control group, women who participate in a weight gain prevention intervention designed to increase self-efficacy, self-regulation, outcome expectations, and family and social support will maintain current body weight during a 12-month period. It is further hypothesized that women in an intervention group led by registered dietitians will have less weight gain during 12 months compared to women in an intervention group led by counselors.

## Methods

### Recruitment, Screening, and Enrollment

Participants were recruited by word-of-mouth, electronic mail messages, and posted flyers from the University of Illinois campus and the Urbana-Champaign (IL, USA) communities. A flow diagram of response, screening, and randomization steps is displayed in Figure 1. A total of 330 women responded to recruitment methods, between June and August 2014. Of these, 266 women met prescreening criteria (appropriate age, body mass index [BMI], and desire to prevent weight gain) and received screening materials including a medical history form, Zung Self-Rating Depression Scale/Status Inventory [33], and informed consent. A total of 146 women returned screening materials, which were reviewed by investigators. One hundred two women met eligibility criteria for participation, and 87 women were randomized, with 81 women completing baseline testing.

The current study included premenopausal women between the ages of 18-45 years with a BMI of >18.5 kg/m^2^. There were no additional criteria for body weight and BMI to ensure participation by women from a range of weight status categories. Further inclusion criteria included eumenorrhea (≥8 menstrual cycles/year), score of <50 on the Zung Self-Rating Depression Scale/Status Inventory [33], and no self-reported metabolic, cardiovascular or musculoskeletal diseases or use of medications or supplements to manage a chronic health condition. Exclusion criteria included women who currently smoked, were pregnant or attempting to become pregnant or were currently lactating. Women using medications influencing weight regulation, such as steroid or thyroid hormones or oral contraceptives, were excluded if use was for <2 months before the start of the study. Gastric bypass surgery was also an exclusion criterion.

The Institutional Review Board (IRB) for the protection of human subjects at the University of Illinois at Urbana-Champaign (UIUC) approved the study protocol (UIUC IRB#14397). Each participant provided written informed consent before study participation.

**Figure 1 figure1:**
[figure not shown]
Diagram of recruitment, enrollment and randomization of participants in a study examining weight gain prevention in young adult and midlife women.

### Study Design

The current study is a 12-month parallel-arm weight gain prevention randomized controlled trial. After enrollment, women were randomized to one of three intervention groups: (1) weight gain prevention intervention delivered by a registered dietitian (RDG); (2) weight gain prevention intervention delivered by a counselor (CSG), or (3) wait-list control (CON) group. The RDG and CSG weight gain prevention interventions are identical in materials and content; the only difference is the credentialing of the individuals leading the intervention. Women in the CON group receive no intervention; upon completion of the 12-month waiting period, these women will be randomized to the RDG group or CSG group and will receive the respective intervention for the next 12-month period.

### Intervention

During the 1-year study, women randomized to the RDG and CSG groups will attend a total of 24, 1-hour nutrition education sessions that are based on effective weight-loss programs/plans which address energy balance through sustainable diet, exercise, and behavior modifications [30,34-39]. These sessions will be held weekly for 16 weeks (months 1-4) and monthly thereafter (months 5-12) [30]. Vegetable consumption, planning ahead for food intake and portion control will be emphasized [34,35], and general nutrition information, eating away from home, food selection, food preparation, and recipe modification also will be addressed [34-37]. Other topics will include fitness and physical activity, culinary skills, breakfast consumption, healthy snacking and beverage choices, nutrient density, family menu planning, and grocery shopping. Problem solving, motivational concerns, and stress management will be encouraged [30,34-39]. Education sessions will relay constructs of the Social Cognitive Theory (SCT) [40].

Education sessions will follow a three-part format. Each session will begin with a brief review of information covered in the previous session and will address participant progress, including successes, challenges and questions. Next, the leader will deliver the nutrition education component of the session using an interactive group discussion format. Participants will be provided with handouts addressing food choices, dietary patterns, menu plans, and other information pertaining to the lesson. Finally, the content for the lesson will be summarized and participants will have a chance to ask questions, address concerns and set specific behavioral goals for the next session. Education sessions will be randomly selected for evaluation by a process observer who will rate the sessions based on investigator-established criteria.

Four registered dietitians will deliver the intervention to women in the RDG group. All women in the RDG group will equally interact with all four registered dietitians during the study. Four counselors will deliver the intervention to women in the CSG group, with these women having equal interaction with all four counselors across the study. The credentials of the professionals delivering the intervention will not be revealed to participants until after completion of the study. The registered dietitians are all female and have been practicing for <5 years. The counselors are all female and are graduate teaching assistants at UIUC in programs unrelated to nutrition or dietetics. Compliance will be defined as attendance of >85% of education sessions. If women are unable to attend an education session, virtual make-up sessions will be offered, along with a quiz. Completion and return of the quiz will indicate that the materials were studied and reviewed and that the participant was compliant.

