### Statistical Analysis

Baseline characteristics of study participants were characterized using descriptive statistics: mean (SD). Participants in the three intervention groups (Treatment) will participate in five data collection sessions at specified intervals (Time). The Shapiro-Wilk test for normality will be used to test for normality and homogeneity of variance within groups; data will be transformed if necessary. Body weight, BMI, waist : hip ratio, FM, BF%, systolic and diastolic blood pressure, serum insulin, glucose, TC, HDL-C, LDL-C, TG, leptin, adiponectin, and resistin will be analyzed as dependent variables. Baseline variables that differ between groups will be included as covariates in the analysis. Dietary intake of macronutrients as estimated from 4-day food records, estimated energy expenditures, eating behaviors, health perceptions, and ratings of SCT mediators also will be compared among groups. A 3 x 5 (3 treatment groups x 5 time intervals) ANOVA with repeated measures on the time factor will be used to assess differences in outcomes within and between treatment groups over time. The group by time interaction will be examined for differences in time trend among intervention groups. Tukey pairwise comparisons will be used in conjunction with ANOVA to detect differences between treatment groups.

Some attrition is expected, as participants may be unable to comply with the intervention or may choose not to continue participation in the study. Participants who withdraw from the intervention will be asked to complete any remaining data collection sessions, and these data will be included in the statistical analyses (ie, intention-to-treat model). Data also will be analyzed using measurements only from those participants who complete all testing sessions. Statistical tests will be two-tailed with significance set at *P*<.01 to reduce the potential for Type I error. All statistical analyses will be conducted using Statistical Package for the Social Sciences (version 22.0, 2013, IBM Corp, Armonk, NY, USA).

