In a recent qualitative study of women who completed a weight-loss intervention conducted by a registered dietitian, women perceived the registered dietitian to be a credible source of nutrition information and found lack of access to a registered dietitian following completion of the intervention to be a barrier to weight-loss maintenance [29]. As a credible source of nutrition information [37], registered dietitians have a specialized skill set to support and encourage sustainable behavior changes to achieve weight management. Registered dietitians are generally regarded as the experts in weight management, but no studies have compared registered dietitians to other health professionals in the delivery of weight management information. The current study will fill this scientific gap by testing the ability of the registered dietitian to promote weight gain prevention as compared to an untrained professional. If registered dietitians are more effective in promoting weight gain prevention, these findings will support the notion that registered dietitians should be at the forefront in helping individuals attain successful weight management.

Women in the qualitative study [29] identified social support, basic nutrition education, accountability to others, self-motivation, mindfulness and awareness of food choices, planning ahead, portion control, and exercise as facilitators to weight loss and weight-loss maintenance while health status changes, environmental pressures, life transitions, absence of social support, lack of accountability, and internal factors were perceived as barriers. Additionally, women expressed their desire for continual contact with the registered dietitian as well as the group support offered by the education sessions [29].

Although there is no standardized definition of weight gain prevention or weight maintenance, a weight change of ±3% from baseline weight will be considered successful weight gain prevention. A 3% change criterion allows for normal day-to-day fluctuations that may result from measurement error, clothing, food consumption, and/or fluid balance [54].

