### Conclusions

The current study targets women who are at greater risk for weight gain compared to men; with the goal to help further the understanding of the determinants of weight gain prevention [29]. This study will fill a scientific gap in testing the ability of a registered dietitian to promote weight gain prevention as compared to another health professional that lacks formal nutrition and dietetics training. Although several studies have explored weight gain prevention with limited success, this may be the first study that targets young adult and midlife women of all weight status categories (normal weight, overweight, obese) and focuses on prospective weight gain prevention. Results of this research will be expected to have implications for policy development and recommendations for decreasing the burden of overweight and obesity in the United States through weight gain prevention.

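### Women in the two led arms share group sessions, yet the named ANOVA treats them as independent, and the dietitian-versus-counselor contrast supports a conclusion about these eight leaders only

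*Protocol article*

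**What the plan says.** **Delivery.** The Intervention section has the nutrition component of each session led "using an interactive group discussion format". On leaders it states "All women in the RDG group will equally interact with all four registered dietitians during the study", and it gives the CSG arm four counselors of its own on the same footing. CON women receive no intervention during the 12 months (Study Design).

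**Analysis.** The Statistical Analysis section states "A 3 x 5 (3 treatment groups x 5 time intervals) ANOVA with repeated measures on the time factor will be used". Tukey comparisons between arms follow, and the section adds "Statistical tests will be two-tailed with significance set at *P*<.01 to reduce the potential for Type I error". No term for session group or leader is named.

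**Comparator.**
- Study Design says of the two led arms that "the only difference is the credentialing of the individuals leading the intervention".
- Intervention describes the counselors as "graduate teaching assistants at UIUC in programs unrelated to nutrition or dietetics".
- Principal Findings describes the test of the dietitian "as compared to an untrained professional".
- Conclusions describes it "as compared to another health professional that lacks formal nutrition and dietetics training".

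Aims and Objectives makes RDG versus CSG a formal hypothesis (less weight gain under dietitians). Principal Findings says that, if dietitians prove more effective, the result would support a leading role for the profession in weight management. Limitations mentions neither shared sessions nor the small set of leaders.

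**The concern.** Women who sit in the same discussion group influence one another and hear the same delivery, so their weight changes may be correlated. The between-subject error term of the named ANOVA assumes that they are not. If they are, the intervals for RDG versus CSG and for led arm versus CON are too narrow, and differences are declared more often than the stated level allows.

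A second limit would remain even with no such correlation. Each arm has its own four leaders and every woman meets all four, so leader set and arm coincide. A difference between RDG and CSG could reflect the credential, or it could reflect these particular people. A reader told that only credentialing differs, and that the comparator is another health professional, would take a positive result as evidence about dietitians against other health professions. The trial does not make that comparison.

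**Working it through.** The article gives no sample-size calculation, ICC, number of session groups or group size, so there is no planned figure to reproduce. What follows sizes the problem under stated assumptions.

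**Inputs from the article**
- 81 women completed baseline testing. At week 8, 75 remained, and 75/81 = 92.6% (printed as 93%).
- 49 women, printed as 89%, remained in the two led arms. 49/54 = 90.7%, 49/55 = 89.1% and 49/56 = 87.5%, so the base is 55. That is 27 or 28 per led arm if split evenly, and 81 − 55 = 26 in CON.
- Three arms, so about 81 − 3 = 78 between-subject degrees of freedom. Tests are two-sided at .01, with Tukey pairwise comparisons.

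**Assumptions (not in the article)**
- ICC of the outcome within a session group: 0.01 to 0.05.
- Group size m: 14 (two groups per arm) or 27 (one group per arm).
- Tukey applied family-wise at .01.

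**Step 1. Variance of RDG minus CSG.** Both arms are clustered, so the factor is DE = 1 + (m − 1) × ICC.
- m = 14: 1 + 13 × 0.01 = 1.13; 1 + 13 × 0.05 = 1.65.
- m = 27: 1 + 26 × 0.01 = 1.26; 1 + 26 × 0.05 = 2.30.

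**Step 2. Variance of led arm minus CON.** Only one side is clustered. With arms of about equal size the factor is (DE + 1)/2.
- m = 14: 2.13/2 = 1.07; 2.65/2 = 1.33.
- m = 27: 2.26/2 = 1.13; 3.30/2 = 1.65.

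**Step 3. Error of the planned comparison.** The Tukey critical value for three groups and 78 df at .01 is 3.00 on the t scale. With independent women, one pairwise comparison then has two-sided error 0.0036. Under clustering it becomes P(|t| > 3.00/√DE) on 78 df.

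| Group size | ICC | DE | 3.00/√DE | Error of RDG v CSG |
|---|---|---|---|---|
| any | 0 | 1.00 | 3.00 | 0.0036 |
| 14 | 0.01 | 1.13 | 2.82 | 0.006 |
| 14 | 0.05 | 1.65 | 2.34 | 0.022 |
| 27 | 0.01 | 1.26 | 2.67 | 0.009 |
| 27 | 0.05 | 2.30 | 1.98 | 0.051 |

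**Step 4. Leaders.** There are four leaders in each led arm and none in common. Every woman in an arm has the same exposure to the same four, so no comparison within an arm carries information on leader differences. A leader term could not be estimated from such contrasts.

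**Step 5. Comparator wording, side by side.** Intervention gives the operational definition: graduate teaching assistants from unrelated programs. Against it:
- The Study Design statement that credentialing is the sole difference does not fit. The arms also differ in the individuals who lead them and in what those individuals do: dietitians in practice against graduate teaching assistants.
- The Conclusions wording does not fit, because nothing in Intervention makes the assistants health professionals. Principal Findings has the same problem where it says the study fills a gap in comparisons of dietitians with other health professionals.

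**The case against.** **The size rests on assumptions.** This stands. The article gives neither an ICC nor the number of groups, and it does not say whether group membership was fixed. Virtual make-up sessions may loosen the grouping. A reader might infer that the standard errors are shown to be too small; the documents support that only if the within-group correlation is positive. At ICC zero the planned test is correct.

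**The error rates could be made to look worse.** A reader might apply a single z-test at 2.576 and conclude that the .01 test runs at 1.5 to 4.5% (groups of 14) or 2.2 to 8.9% (one group of 27). That is not the planned test. Under Tukey at a family-wise .01, the comparison stays below .01 at ICC 0.01 in both scenarios. The understatement of variance is the same either way, because Tukey deals with multiplicity and not with dependence. Nor should the RDG-versus-CSG factors be carried over to comparisons with CON, where they are smaller.

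**Leaders nested in arm are inherent in the question.** This also stands. When provider type is the treatment, leaders must differ between arms. The design softens the problem: averaging over four leaders divides any leader variance by four, all leaders are female, and credentials are concealed from participants. A reader might infer that the ANOVA is wrong for lacking a leader term. It is not; leader variance matters only when the result is extended beyond these eight people. The objection leaves that limit on generalisation untouched.

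**The wording conflict is small.** This is partly right. A reader might count the phrase "as compared to an untrained professional" as a further contradiction, but it is compatible with the Methods if read as untrained in nutrition. The sentence on the profession's leading role is conditional, not a pre-stated result. The sole-difference statement and the health-professional wording still conflict with the Methods.

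**Conclusion.** The point holds in limited form. The named analysis ignores shared sessions in the led arms, so any positive within-group correlation makes the affected intervals too narrow. For ICC 0.01 to 0.05 and groups of 14, the variance is understated 1.13 to 1.65 times for RDG versus CSG and about 1.07 to 1.33 times for a led arm versus CON. With one group of 27 per arm the factors are 1.26 to 2.30 and about 1.13 to 1.65. The Tukey error for RDG versus CSG rises from 0.0036 to 0.006–0.022 or 0.009–0.051. These figures rest on the assumed ICC and group sizes, an even split of the led arms and family-wise use of Tukey.

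Two conclusions need no assumed number. The RDG-versus-CSG contrast cannot separate the credential from the eight leaders. And Study Design and Conclusions describe the comparison in ways that the Intervention section does not support.

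**What to change.** **(a) Analysis.** Record each woman's session group. Report RDG versus CSG and each led arm versus CON with a sensitivity analysis that inflates the variance for ICC 0.01 to 0.05, using the actual group sizes. Fit a random session-group effect, in the led arms only, if there are several stable groups per arm. With one group per arm that effect coincides with arm and cannot be estimated. With two per arm there are four clusters and about 2 degrees of freedom for RDG versus CSG, so the .01 critical t is 9.9 and the model is of little use.

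**(b) Wording.** Describe the comparator throughout as graduate teaching assistants without nutrition training. Remove the sole-difference statement from Study Design and the health-professional wording from Conclusions. In Principal Findings and Conclusions, limit the inference to these leaders, not to dietitians against other health professionals. Add shared sessions and the small set of leaders to Limitations.

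**Cost.** Attendance records, one added analysis and text edits; randomization and visits do not change. The downside is wider intervals and a narrower claim.
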